## Abstract

**Introduction:**

The INflammation and Small Vessel Disease (INSVD) study aims to investigate whether peripheral inflammation, immune (dys)regulation and blood–brain barrier (BBB) permeability relate to disease progression in cerebral small vessel disease (SVD). This research aims to pinpoint specific components of the immune response in SVD relating to disease progression. This could identify biomarkers of SVD progression, as well as potential therapeutic targets to inform the development and repurposing of drugs to reduce or prevent SVD, cognitive decline and vascular dementia.

**Methods and analysis:**

INSVD is a prospective observational multicentre cohort study in individuals with symptomatic SVD. This longitudinal study combines comprehensive immunophenotyping of the peripheral blood immune compartment with advanced neuroimaging markers of SVD and BBB permeability. The main SVD marker of interest is white matter microstructure as determined by diffusion tensor imaging, a valuable marker of disease progression owing to its sensitivity to early alterations to white matter integrity. The research is being conducted in two sites—in the UK (Cambridge) and the Netherlands (Nijmegen)—with each site recruiting 100 participants (total n=200). Participants undergo clinical and cognitive assessments, blood draws, and brain MRI at baseline and 2-year follow-up.

**Ethics and dissemination:**

This study received ethical approval from the local ethics boards (UK: East of England—Cambridge Central Research Ethics Committee (REC) ref: 22/EE/00141, Integrated Research Application System (IRAS) ID: 312 747. Netherlands: Medical Research Ethics Committee (MREC) Oost-Nederland, ref: 2022-13623, NL-number: NL80258.091.22). Written informed consent was obtained from all subjects before the study. Any participant-derived benefits resulting from this research, such as new insights into disease mechanisms or possible novel therapies, will be disseminated to study participants, patient groups and members of the public.

**Trial registration number:**

NCT05746221.

STRENGTHS AND LIMITATIONS OF THIS STUDYDeep immunophenotyping of the peripheral blood immune compartment using state-of-the-art (epi)genetic, transcriptomic and proteomic techniques and functional assays.Longitudinal cohort study design to track disease progression.Advanced neuroimaging techniques to measure and map blood–brain barrier integrity across the brain.Multicentre study with comparable neuroimaging protocols on identical 3T MRI scanners in both sites.However, as deep immunophenotyping is only performed at baseline, this study is not able to assess whether changes in immune cell phenotype are predictive of disease progression.

## Introduction

Cerebral small vessel disease (SVD) is a common condition in older adults characterised by injury to the small penetrating vessels of the brain and accounts for a quarter of all strokes, both intracerebral haemorrhages and lacunar strokes.^1^ As well as resulting in vascular cognitive impairment (VCI),^2 3^ SVD is the major vascular pathology contributing to dementia.^4^ At present, there are no disease-modifying treatments for the resulting VCI, and treatments to reduce SVD are limited to controlling vascular risk factors such as hypertension.^5^ This lack of treatment options is mainly due to an incomplete understanding of the underlying pathophysiology of SVD, although emerging evidence highlights candidate mechanisms such as inflammation and blood-brain barrier (BBB) dysfunction.^6^

The presence of inflammation and immune dysregulation in SVD has been revealed both by blood markers of inflammation,^7^ and by ‘inflammation’ in the central nervous system, observed through neuroimaging (eg, activated microglia in the brain)^8 9^ and neuropathological examination.^10^ Recent exploratory studies showed an association between the cytokine production capacity of circulating monocytes and SVD progression.^11 12^ Innate immune cells can develop a persistent hyperinflammatory phenotype after brief stimulation by epigenetic reprogramming, which has been termed trained immunity.^13^ This also occurs in microglia and can contribute to neuropathology.^14^ We hypothesise that trained circulating and cerebral innate immune cells contribute to SVD progression. However, there remains much uncertainty about the underlying processes linking inflammation to SVD and, in particular, whether inflammation is causally related to disease progression.

Another closely related factor implicated in SVD pathogenesis is BBB permeability.^15–19^ Impaired BBB function is evidenced by albumin leakage into the cerebrospinal fluid or the imaging of gadolinium contrast agent leakage into the brain parenchyma.^15 19^ Normally, the BBB is selective of the blood components allowed to enter the central nervous system. In a dysfunctional state, however, BBB permeability is impaired, leading to the dysregulated leakage of substances into the brain, including harmful substances. Importantly, BBB dysfunction has been reported to be related to chronic unresolved inflammation and *in vivo* studies show a potential shared pathogenic pathway.^20^ As for inflammation, however, it is uncertain whether BBB permeability plays a causal role in SVD pathogenesis, and how it relates to both systemic and central inflammation in patients.

The INflammation and Small Vessel Disease (INSVD) study has been established to address these questions; in particular, to understand the relationship between inflammation and BBB permeability, and their potential relationship with SVD progression. INSVD is a longitudinal cohort study investigating whether systemic inflammation and immune (dys)function, and BBB permeability predict disease progression in SVD, with our primary SVD outcome measure being white matter microstructure as determined by diffusion tensor imaging (DTI), which is a valuable marker of disease progression owing to its sensitivity to early alterations to white matter integrity.^21^

Our overarching aim is to examine in detail the phenotype of circulating immune cells in patients with SVD to identify specific components of the dysregulated immune response which relate to disease progression. This could help identify biomarkers of disease progression and potential therapeutic targets for the development and repurposing of drugs to reduce SVD, VCI and vascular dementia. Study objectives are as follows:

### Primary objective

To determine whether changes in immune cell function and phenotype identified in the systemic circulation predict disease progression in SVD, as measured by DTI-MRI.

### Secondary objectives

To characterise the alteration in immune phenotype occurring in SVD and how these relate to clinical, neurocognitive and imaging parameters.To determine the relationships between systemic immune changes in SVD and BBB leakage.

We hypothesise that activation of the immune system plays a causal role in the progression of SVD, and that mediating processes resulting from this immune activation may involve BBB leakage and inflammation. This progressive damage then compromises structural and functional brain integrity, leading to progressive white matter damage and accelerated VCI.

## Methods and analysis

### Overview

The INSVD study is a prospective multicentre observational cohort study in patients with SVD. The research will be conducted at two sites—Cambridge (UK) and Nijmegen (The Netherlands)—each recruiting 100 participants (total n=200). At baseline and 2-year follow-up, participants undergo clinical and cognitive assessments, blood draw and brain MRI. Follow-up will be continued for the next 6 years to track incident clinical events, among others (figure 1). Study recruitment began in August 2022 and study visits (baseline and 2-year follow-up) are projected to be completed by August 2026.

**Figure 1 F1:**
[figure not shown]
Overview of study components.

### Participants

#### Inclusion criteria

The study recruits individuals aged 40 and above with symptomatic SVD—this is defined as having a lacune on MRI according to the Standards for Reporting Vascular Changes on Neuroimaging (STRIVE) guidelines,^22 23^ in addition to at least one of the three following clinical presentations: (a) clinical lacunar stroke syndrome; (b) symptoms of cognitive impairment presumed to be due to SVD and (c) gait/motor impairment presumed to be due to SVD. Baseline study visits are performed after a minimum interval of 3 months after participants’ most recent stroke and at least 1 month after any systemic infection or vaccination.

#### Exclusion criteria

Potential participants are excluded if they have any MRI contraindication, or an estimated glomerular filtration rate (eGFR) <60 mL/min/1.73 m^2^ (UK) or <30 mL/min/1.73 m^2^ (Netherlands) within the past 3 months (figure 2). If eGFR has not been assessed within the last 3 months, this is measured as part of the research procedure. Other exclusion criteria include strokes caused by factors other than SVD (eg, cardioembolic source, carotid or vertebral artery stenosis >50%), another diagnosed chronic neurological condition (eg, Alzheimer’s disease, Parkinson’s disease), myocardial infarction in the past year, vasculitis, autoimmune or autoinflammatory disease, treatment with immunomodulating drugs, known monogenic causes of SVD, or limited life expectancy due to another illness or chronic condition which would make the 2-year follow-up difficult (eg, widespread malignancy).

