#### Blood samples

Non-fasting, venous blood samples are drawn at baseline and 2-year follow-up by qualified clinical personnel. Blood withdrawal is performed before MRI to ensure that the injected gadolinium-based MRI contrast agent does not interfere with laboratory tests.^36^ Blood samples are collected at approximately the same time of day for all participants to minimise circadian-related variation in inflammatory and coagulation markers.^37^ At baseline, blood is collected in EDTA tubes for plasma, serum tubes for serum and BD Vacutainer CPT tubes (BD Biosciences) for whole blood and PBMCs. Blood tubes are stored at room temperature and processed within 2 hours after collection for the following procedures:

PBMCs are isolated using sodium heparin CPT tubes following manufacturer recommendations and freshly stimulated for 24 hours with the TLR-4 agonist lipopolysaccharide (LPS), with the TLR-2 agonist Pam3Cys-Ser-(Lys)4, with LPS plus the inflammasome activator Nigericin, or with RPMI buffer as control. Supernatants are stored at −80°C for future analysis of cytokines and chemokines.Comprehensive immunophenotyping of fresh whole blood is performed by using Cytometry by Time-Of-Flight (CyTOF).Isolated PBMCs are viably frozen to allow future single-cell RNA sequencing (scRNA-seq), Assay of Transposase Accessible Chromatin with high-throughput sequencing (ATAC-seq) and regulatory T cell (Treg) suppression assays. ScRNA-seq, ATAC-seq and Treg suppression assays will be performed after completion of the study in subgroups of patients with the highest and lowest progression rates of SVD.A panel of circulating inflammatory markers is measured in serum using the Olink proteomics platform (Olink Proteomics AB, Uppsala, Sweden).

At 2-year follow-up, blood will be collected in EDTA tubes and processed according to manufacturer’s instructions. Plasma will be stored at −80°C for future analysis of circulating inflammatory and coagulation markers.

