### Data analysis

Peak height of the MD histogram was selected as the primary endpoint, given our past demonstration that it is the most sensitive DTI marker for SVD progression.^43^ Based on longitudinal MRI data from the SCANS study, the yearly rate of change of MD peak height was −3.72×10^−4^ mm^2^/s (SD 3.12×10^−5^), which corresponds to an annual percentage change of −2.44%.^43^ This would equate to a change of −4.88% over the 2-year follow-up period of the INSVD study.

Our primary analysis will test whether baseline measures of inflammatory and immune markers predict SVD progression as measured by MD peak height. We assume a linear relationship between baseline levels of coagulation and inflammatory markers and the change in MD peak height. Therefore, we will run linear regression models and adjust for age, sex, education and other conventional MRI markers of SVD, where appropriate.

As our secondary objectives, we will assess (1) the relationship between inflammatory and immune markers and BBB permeability, both globally (cortical and subcortical volumes) and regionally (hotspot volumes) and (2) whether baseline levels of inflammatory and immune markers are associated with other imaging parameters, as well as cognitive and clinical outcomes. Similar to our primary analyses, we will conduct linear regression modelling to test these associations.

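### Baseline eGFR, obtained for everyone and admitted over a wider range in Nijmegen, is not a stated covariate; if kidney function relates to both serum markers and progression, modest confounding remains that a site term would not fully remove.

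*Protocol article*

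**What the plan says.** Exclusion criteria: participants are excluded for an "estimated glomerular filtration rate (eGFR) <60 mL/min/1.73 m^2^ (UK) or <30 mL/min/1.73 m^2^ (Netherlands) within the past 3 months". The value is to be available for everyone: "If eGFR has not been assessed within the last 3 months, this is measured as part of the research procedure".

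Data analysis: "Our primary analysis will test whether baseline measures of inflammatory and immune markers predict SVD progression as measured by MD peak height". For this, "we will run linear regression models and adjust for age, sex, education and other conventional MRI markers of SVD, where appropriate". Neither eGFR nor site is named. For the secondary objectives (BBB permeability, other imaging, cognition, clinical outcomes): "Similar to our primary analyses, we will conduct linear regression modelling to test these associations".

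Blood samples: the exposures are of two kinds. One is proteins in the circulation: "A panel of circulating inflammatory markers is measured in serum using the Olink proteomics platform". The other is cellular or ex vivo: cytokine release by stimulated PBMCs, and CyTOF phenotyping of whole blood.

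The article does not discuss renal clearance of these proteins, gives no relation between eGFR and MD peak height, and does not say how many Nijmegen participants are expected in the 30 to below 60 band.

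**The concern.** The eligibility rule makes the range of one baseline variable differ by site: everyone with an eGFR of 30 to below 60 comes from Nijmegen. That variable is obtained at entry, but it is outside the covariate set the article states. If lower eGFR goes with higher circulating inflammatory proteins and also with faster white matter change, it is a common cause of exposure and outcome, and the regression attributes part of its effect to the marker.

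The study aims to find biomarkers and therapeutic targets, so a serum protein that partly reflects kidney function would be a misleading lead. Site adjustment, even if added, takes out only the difference in mean eGFR between the centres. The variation within each centre stays.

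**Working it through.** **The plan's own figure.** Fisher's formula for r = 0.22, two-sided α = 0.05, 80% power: n = ((1.960 + 0.842)/atanh 0.22)² + 3 = 159.9, so 160; 160/0.80 = 200. Both stated figures reproduce. At n = 160 the smallest significant |r| is tanh(1.96/√157) = 0.155.

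**Inputs from the article.** Two sites of 100; 160 evaluable (80 per site if losses are equal); eGFR limits of 60 and 30; planned r = 0.22.

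**Assumed inputs (the article gives none).**
- eGFR: mean 78, SD 14, cut at 60 in Cambridge; mean 72, SD 18, cut at 30 in Nijmegen. About 25% of Nijmegen participants then fall below 60.
- Marker-eGFR slope a = 0.2, 0.3 or 0.5 SD; progression-eGFR slope b = 0.1 or 0.2 SD. Signs are dropped below.
- eGFR-age correlation 0.5.
- No true immune effect.

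**Approximate formula.** With unit residual variances, and V the share of eGFR variance left after the covariates:

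r ≈ abV / √[(1 + a²V)(1 + b²V)]

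With site only, V is taken as about 1. With age as well, V = 1 − 0.5² = 0.75. The false-positive rate is P(|Z + δ| > 1.96), where δ = √(160 − 3 − k) × atanh r and k is the number of covariates (k = 2, so √155 = 12.45, for site and age).

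Largest case with site and age (a = 0.5, b = 0.2): r = 0.075/√(1.1875 × 1.03) = 0.068; δ = 0.85; rate = 0.132 + 0.003 = 13.5%.

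| a | b | Site only, simulated: r | rate | Site + age, formula: r | rate |
|---|---|---|---|---|---|
| 0.2 | 0.1 | 0.019 | 5.5% | 0.015 | 5.4% |
| 0.2 | 0.2 | 0.036 | 7.5% | 0.029 | 6.5% |
| 0.3 | 0.1 | 0.024 | 6.1% | 0.022 | 5.8% |
| 0.3 | 0.2 | 0.053 | 10.1% | 0.043 | 8.3% |
| 0.5 | 0.1 | 0.045 | 7.3% | 0.034 | 7.1% |
| 0.5 | 0.2 | 0.086 | 19.6% | 0.068 | 13.5% |

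The simulations used 4,000 data sets per scenario. Simulation with site and age gives the same picture as the formula: r about 0.01 to 0.07, and a rate of about 6% to 8% in five scenarios and 14% in the strongest. With eGFR in the model, r is about 0 and the rate about 5%.

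**Second construction.** A yes/no indicator for eGFR 30 to below 60 in Nijmegen only, 80 + 80 participants, 6,000 runs, age not modelled:

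| Share of Nijmegen in band | Marker shift | Progression shift | No adjustment: r, rate | Site: r, rate | Site + eGFR: r, rate |
|---|---|---|---|---|---|
| 20% | 0.8 SD | 0.5 SD | 0.034, 7.1% | 0.031, 6.6% | 0.000, 5.1% |
| 40% | 1.0 SD | 0.8 SD | 0.112, 29.4% | 0.086, 19.4% | −0.001, 5.1% |
| 30% | 0.8 SD | 0 | −0.002, 5.0% | −0.002, 4.8% | −0.002, 4.8% |

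The last row is the control: a raised marker with no kidney-progression link produces no bias.

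**How much is due to the unequal thresholds?** On the assumed distributions, the average within-site variance of eGFR is about 222. If Nijmegen were also cut at 60 it would be about 156, and 156/222 = 70%. Most of the variation that could confound is therefore present whatever the lower limit in Nijmegen.

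**The case against.** The strongest reply is that this is a condensed article, its covariate list carries the qualifier that adjustment is made where appropriate, and a fuller list may stand in an analysis plan not shown. That stands in part: nothing in the article is contradictory, and eGFR may already be planned. But the article does state a covariate set, and it also states site-specific eligibility on a variable outside that set. Naming the variable is a specific, cheap improvement.

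Other limits stand in full. The links of kidney function to the markers and to progression are not in the documents. The link to progression must persist after age, sex, education and MRI markers; the figures above allow for age only, and the remaining covariates could shrink them further. The mechanism bears mainly on serum proteins. It does not directly affect stimulated PBMC cytokines, on which the sample size partly rests, or CyTOF phenotypes.

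A reader might infer more than the documents support:
- **That reduced clearance by itself mimics immune-driven progression.** It does not; the control row shows no bias without a kidney-progression link.
- **That the different thresholds are the cause.** They widen the eGFR range at one site, but about 70% of the within-site variance would remain under a common limit of 60.
- **That a false signal would be concentrated in Nijmegen and be read as a site difference.** No per-site result has been shown, and the Data analysis section describes no comparison between sites.
- **That kidney function goes otherwise unrecorded.** Clinical assessment covers medical history from records, and its risk-factor list is given by example only.

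**Conclusion.** The point holds as a modest, conditional one. The documentary facts are firm: the 30 to below 60 band is open in Nijmegen only, a recent eGFR is obtained for all, and it is not a named covariate. Whether this biases anything depends on two links the article does not quantify.

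On the assumed ranges, with site and age in the model, the spurious correlation is at most about 0.07, roughly a third of the planned 0.22 (0.07/0.22 = 32%) and below the 0.155 needed for significance. It would not by itself produce the planned effect. It would raise the false-positive rate per serum marker from 5% to about 6% to 8% in most scenarios and 14% in the strongest (about 20% without age). Including eGFR brings it back to about 5%.

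**What to change.** In the Data analysis section or the analysis plan, name baseline eGFR, as a continuous variable using the value obtained for eligibility, as a covariate in the primary and secondary models of circulating (serum) markers. For the cellular and ex vivo markers, report it as a sensitivity adjustment. Confirm that the numerical value is kept in the study data, and not only the eligibility decision.

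The cost is one degree of freedom and a few words; no new measurement and no change in sample size. The downside is possible slight over-adjustment if eGFR partly reflects the same vascular disease, so showing the estimates with and without it is sensible.

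An analysis restricted to eGFR of 60 or above at both sites is optional. On the assumptions above it drops about 20 of 160 participants (25% of 80) and lowers power from 80% to about 74%. The eligibility thresholds themselves are not at issue here.

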**Figure 2 F2:**
[figure not shown]
Study flow chart; based on planned sample sizes. INSVD, INflammation and Small Vessel Disease.

#### Participant recruitment

At the Cambridge site, participants are screened and recruited from the clinical stroke service at Cambridge University Hospitals National Health Service Foundation Trust and patient registers of patients with SVD enrolled in previous research studies. Screening is conducted through electronic hospital records, discussions with the patient about relevant medical history, and through the local MRI safety questionnaire. ECG and carotid artery duplex scans have been performed as part of ischaemic stroke workup and are used to rule out stroke causes other than SVD.

At the Nijmegen site, participants are recruited from the Radboud University Nijmegen Diffusion tensor and Magnetic resonance imaging Cohort (RUN DMC) study,^24^ and the neurology outpatient clinic at Radboud University Medical Centre. Screening involves reviewing electronic hospital records and discussing medical history with the patient. ECG and carotid artery duplex scans are included as part of screening procedures, in case information on atrial fibrillation and large artery disease are not up to date or readily available from medical records.

#### Sample size calculation

Power calculations were based on previous findings demonstrating associations between circulating IL-6 and SVD progression,^25^ and our pilot data showing a correlation between IL-6 production in peripheral blood mononuclear cells (PBMC; after ex vivo toll-like receptor-2 (TLR2) stimulation) and SVD progression (white matter hyperintensity (WMH) progression) of r=0.22.^11^ To detect a correlation of r=0.22 at α=0.05 with 80% power (two-tailed test with Fisher formula), 160 participants with evaluable datasets are needed. To account for dropouts and unusable data (eg, failed MRI quality check) estimated at 20%, we are recruiting 200 participants.

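### The stated 80% power is for one marker tested once against WMH progression; it does not describe the primary analysis, which tests several markers against change in MD peak height

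*Protocol article*

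**What the plan says.** The section on sample size calculation sets the target: "To detect a correlation of r=0.22 at α=0.05 with 80% power (two-tailed test with Fisher formula), 160 participants with evaluable datasets are needed". Allowing 20% for dropout and unusable data gives 200 recruited. The effect size is pilot data relating IL-6 production by PBMC after TLR2 stimulation to "SVD progression (white matter hyperintensity (WMH) progression) of r=0.22". Earlier findings on circulating IL-6 are cited as further background.

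The Data analysis section names MD histogram peak height as the primary endpoint and continues: "Our primary analysis will test whether baseline measures of inflammatory and immune markers predict SVD progression as measured by MD peak height". The next sentence assumes linearity for coagulation and inflammatory markers, and the models are linear regressions adjusted, where appropriate, for age, sex, education and conventional MRI markers. No single marker is singled out there or in the primary objective.

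The Blood samples section lists the baseline sources for the whole cohort: PBMC supernatants under three stimuli and a control, kept for cytokine and chemokine measurement; CyTOF on whole blood; and "A panel of circulating inflammatory markers is measured in serum using the Olink proteomics platform". It gives no count of analytes.

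**The concern.** The test that was sized and the primary analysis differ in two respects.

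- **Predictor.** The calculation has one marker and spends the whole 0.05 on it. The primary analysis has several markers.
- **Outcome.** The r of 0.22 is for WMH progression. The primary endpoint is MD peak height, for which the article gives no correlation with any immune marker.

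A reader who sees 80% power next to a primary analysis will take it as the power of that analysis. At stake is how the primary result is read. A positive marker tested at 0.05 among many is weaker evidence than the sample size section suggests. A null result after correction could come from a study with far less than 80% power for the effect it was sized on.

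**Working it through.** **Inputs from the article:** r=0.22, two-sided α=0.05, power 80%, Fisher formula, 160 evaluable, 20% loss, 200 recruited (Sample size calculation). **Assumed:** the number of primary markers K, shown for 2, 6, 10 and 50; Bonferroni as the correction; independent true nulls for the false-positive figures. The Fisher formula is for a simple correlation, so covariate adjustment is left out here, as it is in the article's own calculation.

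**1. The plan's own figure.** N = ((z₀.₉₇₅ + z₀.₈₀)/atanh(r))² + 3 = ((1.960 + 0.842)/0.2237)² + 3 = 159.9, so 160. Then 160/(1 − 0.20) = 200. Both figures reproduce, for one test.

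**2. Several markers at n=160 and r=0.22.** The standardised effect is atanh(0.22) × √157 = 0.2237 × 12.53 = 2.802.

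- Bonferroni power per marker = Φ(2.802 − z), where z is the normal quantile at 1 − 0.05/(2K).
- r detectable with 80% power = tanh((z + 0.842)/12.53).
- Chance of at least one false positive with no correction = 1 − 0.95^K.

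| K (assumed) | z | Bonferroni power at r=0.22 | r detectable with 80% power | Uncorrected chance of ≥1 false positive |
|---|---|---|---|---|
| 1 | 1.960 | 80% | 0.22 | 5% |
| 2 | 2.241 | 71% | 0.24 | 10% |
| 6 | 2.638 | 57% | 0.27 | 26% |
| 10 | 2.807 | 50% | 0.28 | 40% |
| 50 | 3.291 | 31% | 0.32 | 92% |

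The two right-hand consequences are alternatives. With no correction, each marker is still tested at 0.05 and keeps 80% power if r=0.22 applies to it; what goes is control across the family. With correction, family-wise control is kept and power falls.

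**3. Change of outcome.** For one test at 0.05 and n=160, power = Φ(atanh(r) × 12.53 − 1.960). If the correlation with MD peak height were 0.15, this is Φ(1.894 − 1.960) = 47%. If it were 0.25, it is Φ(3.200 − 1.960) = 89%. The article does not say where in such a range the correlation lies.

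**The case against.** The strongest reply is that this is a condensed article about an observational cohort whose overarching aim is to identify components of the immune response. The correction method and the ranking of markers commonly sit in an analysis plan that is not shown. That stands: the absence of a multiplicity rule is not the point made here. What remains is that the sample size and the scope of the primary analysis are both stated, and they do not match. A correction specified elsewhere would not restore 80% power at r=0.22 with 160 participants under the Bonferroni calculation above.

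Several stronger readings are tempting, and the documents do not support them.

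- *That both power and error rate fail.* The sample size section promises 0.05 and 80% for a single correlation and never claims 5% family-wise error. One or the other is lost, depending on whether a correction is applied.
- *That a chance finding is almost certain.* This needs a large family: 92% at K=50, but 26% at K=6.
- *That the Blood samples section implies at least six tests.* It gives no analyte count. Six is an illustration, for example three stimuli by two analytes.
- *That every assay belongs to the family.* Single-cell RNA sequencing, ATAC-seq and the Treg suppression assays are planned only in subgroups with the highest and lowest progression, so they are not whole-cohort predictors in this regression.
- *That the change of endpoint lowers power.* The article calls MD peak height the most sensitive DTI marker of progression, so the correlation may be larger or smaller than 0.22.

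Bonferroni with independence is also close to the worst case. Correlated markers or false discovery rate control would soften the figures in the table.

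**Conclusion.** The point holds in this form. The 80% power is right for one two-sided test at 0.05 of r=0.22, and it is not the power of the primary analysis as the article describes it. Under Bonferroni, any family of two or more markers loses either the 80% power at r=0.22 or 5% family-wise control at n=160. The size of the loss depends on K, which the article does not give: it runs from 71% power with two markers to 31% with fifty, or, left uncorrected, from a 10% to a 92% chance of at least one false positive. Separately, because r=0.22 was observed for WMH progression, the power for MD peak height is unsupported in either direction. No error was found in the arithmetic of the 160 or the 200.

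**What to change.** In the sample size section, say that the 80% power applies to one marker tested at α=0.05, and that r=0.22 is carried over from WMH progression as an assumption for MD peak height. Then, before follow-up outcomes are analysed, do one of the following:

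- (a) state the number of primary markers and the correction, and give the detectable r or the power at n=160; or
- (b) name the sized marker, TLR2-stimulated IL-6 production, as the one confirmatory test against 2-year change in MD peak height, and report the other markers as secondary or exploratory under false discovery rate control.

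Neither needs more participants or assays. The cost of (a) is a less favourable stated power or detectable r. The cost of (b) is that the other markers lose confirmatory status, including immune phenotype, which the primary objective covers; that objective would need to be reworded to match. Option (a) fits the study's aims with less disturbance.
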